## Trial design {8}

A randomised, parallel groups, double-blind, two-arms, sham-controlled trial will be implemented to investigate the effects of the PPC-M1 PAS in add-on to RAT. Neurologists, PM&R, engineers, psychologists and physiotherapists were involved in the study design. No patient or public participation was foreseen.

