### Outcomes {12}

The primary outcome of the study is the difference between the Exp group and Ctrl group in functional mobility of the UL. It will be measured using the Fugl-Meyer Assessment Scale for Upper Extremity (FMA-UE).

Secondly, we will investigate clinical, kinematic and neurophysiological changes between the two groups using:The Box and Block Test to assess manual dexterity.The Modified Ashworth Scale to assess spasticity.Kinematics variables, recorded via inertial measurement units and motion analysis during three-reaching tasks and the Box-and-Block test, to assess functional movements.TMS-evoked potentials, recorded via TMS-EEG, to assess cortical reactivity.TRSP, recorded via TMS-EEG, to assess oscillatory dynamics of the PPC and M1.PLV, recorded via TMS-EEG, to assess the actual connectivity between a targeted area with respect to the entire neural network.

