### Sample size {14}

According to an a priori Power analysis, considering 80% power and a 95% CI, 32 patients would be needed for necessary sample size, based on previously published work on cortical plastic changes induced by neurostimulation via TMS [14].

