### Data collection and management

#### Plans for assessment and collection of outcomes {18a}

Clinical, instrumental and neurophysiological evaluation will be assessed at baseline (T0); after the 3 weeks of treatment (T1); and after 7 weeks from the baseline as a follow-up—4 weeks from the end of the treatment—(T2).

Demographics data (i.e. age, gender, lesion site) will be acquired through clinical documentation provided during the screening procedure. All collected data will be stored in an online data sheet protected with a password. To promote data quality, all raters were specifically trained in the administration of the clinical scales and in kinematics evaluation.

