### Statistical methods

#### Statistical methods for primary and secondary outcomes {20a}

Data characterised by normal distribution will be expressed as means with standard deviations. Parameters not normally distributed will be expressed as medians with the interquartile ranges. Parametric data will be analysed with a 3 × 2 mixed model ANOVA considering time (TIME: T0 vs T1 vs T2) and group allocation (GROUP: Real vs Ctrl) as within and between factors, respectively, with *α* = 0.05. Each significant interaction (TIME × GROUP) will be further explored with the Bonferroni post hoc correction. Nonparametric data will be investigated with Friedman’s test and, if *p* < 0.05, with Wilcoxon test such as post hoc. Correlations (Pearson for normal distributed data or Spearman for non-normal distributed data) and regression analysis will be performed between clinical, kinematic and neurophysiological data to investigate casual and causal interaction respectively. Sub-group analysis can be performed after severity stratification (i.e. FMA < 17).

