## Discussion

The objective of the current study protocol is to test the effects of a PPC-M1 PAS in add-on to 15 consecutive sessions of RAT on motor function of the upper limb in chronic stroke via a RCT with a multimodal investigation (clinical, kinematic and neurophysiological). In line with the aim of the current study protocol, Tang et al. in their meta-analysis reported how using high-frequency TMS on the ipsilateral hemisphere is beneficial for motor function, hand strength and hand dexterity in patients diagnosed with sub-acute stroke [29]. Similarly, a network meta-analysis on non-conventional therapies for motor recovery after a stroke reported the high-frequency repetitive transcranial magnetic stimulation as one of the most effective treatments [30]. Similarly, to our protocol, a very recent study tested the combination of another form of non-invasive brain stimulation (dual-tDCS) combined with robot-assisted therapy in chronic stroke finding a positive effect on motor functions in the subgroup of patients with severe cortico-spinal damage treated with real stimulation with respect to the control [31]. Based on the abovementioned scientific evidence, we expect that the stimulation of the central nervous system by the augmented feedback generated by robot-assisted therapy, during the neuromodulation window induced by PAS, can promote a cortical reorganisation which in turn results in a clinical improvement. Therefore, the combination of the two approaches should generate a boost effect on functional motor recovery of UL.

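### Regression between measured outcomes is given a causal purpose that randomising the stimulation arm does not support

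*Protocol article*

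**What the plan says.** The section on statistical methods for primary and secondary outcomes {20a} of the protocol article names two methods for relating the three families of measurement. The first is correlation: "Correlations (Pearson for normal distributed data or Spearman for non-normal distributed data". The second follows in the same sentence: "regression analysis will be performed between clinical, kinematic and neurophysiological data to investigate casual and causal interaction respectively". The sentence lists two methods and two aims and matches them in order, so correlation goes with the casual aim and regression with the causal one.

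Three other places fix what these variables are:

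- **Trial design {8}:** the assigned factor is the stimulation. The section opens: "A randomised, parallel groups, double-blind, two-arms, sham-controlled trial will be implemented to investigate the effects of the PPC-M1 PAS in add-on to RAT".
- **Outcomes {12}:** for the secondary measures, "we will investigate clinical, kinematic and neurophysiological changes between the two groups using", followed by Box and Block, Ashworth, kinematics, TMS-evoked potentials, TRSP and PLV. FMA-UE is the primary outcome.
- **Plans for assessment {18a}:** "Clinical, instrumental and neurophysiological evaluation will be assessed at baseline (T0"), and again at T1 and T2, with all domains on the same visit schedule.

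The Discussion gives the working hypothesis, that training during the window opened by stimulation "can promote a cortical reorganisation which in turn results in a clinical improvement".

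**The concern.** Randomisation supports a causal reading of arm on each outcome. It does not support one of PLV on FMA-UE, or of a kinematic variable on a clinical score, because nobody was assigned a value of PLV or of a kinematic variable. Two patients who differ in cortical connectivity may also differ in arm, severity, lesion and time since stroke, and each of these can move both measures. A patient who uses the limb more may also change cortically as a result, which is the reverse direction.

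The article nevertheless separates regression from correlation by what each can show, and places causation on the regression side. This regression is also the only stated analysis that links neurophysiological to clinical measures. A significant slope could therefore be read as evidence of a mechanism when it is evidence of association only.

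**Working it through.** **Inputs from the article.** Planned sample size 32 (Sample size {14}: "considering 80% power and a 95% CI, 32 patients would be needed for necessary sample size"). Significance level: "with *α* = 0.05", stated for the ANOVA; I take it as two-sided. The article gives no effect size, SD or correlation between measures, and no figure of its own on this point to reproduce.

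**Step 1: is regression more causal than correlation here?** With one predictor, the test of a zero slope and the test of a zero Pearson correlation share one statistic, t = r√(n − 2)/√(1 − r²), and so one p-value. In one simulated data set of 32 the p-value was 0.5526 for the correlation, for y regressed on x and for x regressed on y. The test cannot tell direction, so the contrast drawn in {20a} has no statistical basis for a single predictor. Adding covariates changes the estimate, but becomes a causal argument only with an adjustment set, a time order and an assumption of no unmeasured confounding. The shared visit schedule supplies no time order between the domains.

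**Step 2: how often would an unrelated pair look related?** This is an illustration only. Assumptions: 16 patients per arm, arms pooled, no covariates, within-arm SD of 1 for both measures, and no causal path between them.

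*Arm as the only common cause.* If treatment shifts both measures by d SD and arms are equal in size, the between-arm covariance is d²/4 and each total variance is 1 + d²/4. The expected correlation is

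r = (d²/4)/(1 + d²/4).

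- d = 1.0: r = 0.25/1.25 = 0.20.
- d = 1.5: r = 0.5625/1.5625 = 0.36.

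*An unmeasured common cause.* If both measures share a cause such as severity that induces a within-arm correlation of 0.5, no treatment effect is needed for an association to appear.

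Share of simulated trials with p < 0.05:

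| Assumed situation, no causal link | Unadjusted | Adjusted for arm |
|---|---|---|
| No common cause | about 5% | about 5% |
| Arm shifts both by 1.0 SD | about 20% | about 5% |
| Arm shifts both by 1.5 SD | about 57% | about 5% |
| Unmeasured cause, correlation 0.5 | about 86% | about 84% |
| Arm (1.0 SD) and unmeasured cause | about 97% | about 84% |

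**Reading.** If stimulation works on both measures, a pooled unadjusted regression gains apparent support through treatment alone, and adjusting for arm removes that part. Adjusting for arm does almost nothing against a shared cause that is not in the model. Baseline FMA-UE would remove only the part of severity that it captures.

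**The case against.** **The article specifies no model.** It names no dependent variable, covariate, time point or pooling rule, and such detail is commonly left to the full protocol or analysis plan. This stands. A reader might infer that the plan leaves out arm and baseline, but the text is silent and does not say so. The point therefore rests on the stated purpose of the regression, which is in the article, and not on missing covariates.

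**The verb is only to investigate.** This also stands. A reader might infer that the article declares regression to show causation; it does not go that far. The wording is loose, and a directional or predictive meaning is possible. The explicit contrast with correlation still makes the causal reading the natural one, and the aim is out of reach for this analysis whichever verb is used.

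**The Discussion states a prior hypothesis.** Agreed. A reader might infer that the regression will be used to claim that cortical change produced the clinical gain. Nothing in the article ties that sentence to the regression or commits the investigators to a mediation claim.

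**The percentages rest on assumed inputs.** True. The shifts of 1.0 and 1.5 SD and the shared correlation of 0.5 appear nowhere in the article. Even at 1.0 SD about 80% of such trials would not be significant. The figures show the mechanism; they do not measure a defect in this trial.

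**Covariates do not cure confounding.** Correct, as the 84% rows show. This is why the wording is the essential part of the remedy.

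**Conclusion.** The point holds in a limited form. The article assigns regression among measured outcomes a causal purpose that randomising the stimulation does not support, and no other section supplies a mediation model, time order or identifying assumption that would. The conclusion follows from the design and the stated purpose and needs no numerical assumption.

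The size is illustrative: false support in about 20% to 57% of trials for assumed shifts of 1.0 to 1.5 SD in a pooled, unadjusted model, and far more under strong unmeasured confounding.

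Severity is minor to moderate. The primary FMA-UE comparison and the between-group comparisons of secondary outcomes do not depend on this regression. What is affected is the strength of any mechanistic statement drawn from it.

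**What to change.** In {20a}, describe both correlation and regression among clinical, kinematic and neurophysiological measures as exploratory association, and drop the causal aim. Include randomised arm and baseline FMA-UE in the regression, report estimates with confidence intervals, and state that no causal or mediation conclusion will be drawn from it. The covariates remove the association created by treatment and part of that due to severity; they do not make the regression causal.

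If a mechanistic claim is wanted, the alternative is a pre-specified mediation analysis (arm, neurophysiological change, FMA-UE change) with its confounders, time order and no-unmeasured-confounding assumption written down, and its low precision at 32 patients acknowledged.

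The cost is a change of wording, two model terms that are already collected, and a weaker mechanistic claim. No further patients or measurements are needed.

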#### Interim analyses {21b}

Interim analysis will be performed only once when the outcomes of 20 patients will be made available. The sub-investigator designated to manage randomisation will perform the analysis according to the methodology described in the statistical planning. The results will be discussed with the PI. In case of differences in demographic and clinical characteristics between the two groups, the further recruitment will follow a pseudo-randomisation taking into account the balance in the following factors: age, sex, lesion side, stroke onset and UL severity.

#### Methods for additional analyses (e.g. subgroup analyses) {20b}

Sub-group analyses are not foreseen.

#### Methods in analysis to handle protocol non-adherence and any statistical methods to handle missing data {20c}

Handling of missing data will be performed with multiple imputation. Namely, missing values will be replaced with a set of plausible values containing the natural variability and uncertainty of the right values.

#### Plans to give access to the full protocol, participant-level data and statistical code {31c}

The study protocol and data analysis will be available from the corresponding author upon request.

#### Composition of the data monitoring committee, its role and reporting structure {21a}

Data monitoring committee is not formally planned for this study for the low-risk factors. The PI is responsible to provide the clinical trials centre (CTC) with a safety annual report, including data about the current recruitment status as well as information about eventual occurring major complications and adverse events. The CTC is an independent internal research board of IRCCS Santa Lucia Foundation of Rome.

#### Adverse event reporting and harms {22}

Expected harms concern exceptional adverse events (AEs) due to TMS that are reported in the literature: (1) skin burn and (2) seizures (of note, seizures have been reported using repetitive TMS in about 10 human subjects, out of tens of thousands tested all over the world), and minor AEs due to TMS or RAT reported in the literature: (1) transient headache, (2) transient dizziness, (3) transient nausea, (4) phosphene-like visual phenomenon if the stimulation will be switched on or off rapidly, (5) paretic upper limb pain.

In the event of an AE, NIBSU staff will provide first aid and notify the event to the emergency office of the IRCCS Fondazione Santa Lucia in Rome. The office, in case of need, will provide specialised assistance in emergency care and management of the case.

All AEs, expected and unexpected, will be reported immediately and in an annual report to the CTC by the PI. All eventually AEs will be collected and reported in the disseminations.

#### Frequency and plans for auditing trial conduct {23}

The steering committee will perform 6-month audits during the entire duration of the trial. For each audit will be evaluated the congruousness with respect to trial procedures, data management and timescale. Any critical issues will be discussed by the steering committee and communicated to interested co-investigator/s. Additionally, auditing will be performed, without anticipated communication, by the CTC board.

#### Plans for communicating important protocol amendments to relevant parties (e.g. trial participants, ethical committees) {25}

All modifications about protocol and procedures must first be approved, by amendment, by the independent Ethics Committee of the Santa Lucia Foundation Hospital. If approved, the changes will be communicated and reported in the online registration of the protocol. All investigators and participants will be immediately informed about the modifications.

### Dissemination plans {31a}

The results dissemination will be carried out by investigators of the study. The results will be published in peer-reviewed journals and reported in conferences presentations and/or posters. After publication, it could be published via dedicated websites/forums and/or social media. The sponsor does not have any role regarding execution, analyses, interpretation of the data, or in dissemination of results.

## Discussion

The objective of the current study protocol is to test the effects of a PPC-M1 PAS in add-on to 15 consecutive sessions of RAT on motor function of the upper limb in chronic stroke via a RCT with a multimodal investigation (clinical, kinematic and neurophysiological). In line with the aim of the current study protocol, Tang et al. in their meta-analysis reported how using high-frequency TMS on the ipsilateral hemisphere is beneficial for motor function, hand strength and hand dexterity in patients diagnosed with sub-acute stroke [29]. Similarly, a network meta-analysis on non-conventional therapies for motor recovery after a stroke reported the high-frequency repetitive transcranial magnetic stimulation as one of the most effective treatments [30]. Similarly, to our protocol, a very recent study tested the combination of another form of non-invasive brain stimulation (dual-tDCS) combined with robot-assisted therapy in chronic stroke finding a positive effect on motor functions in the subgroup of patients with severe cortico-spinal damage treated with real stimulation with respect to the control [31]. Based on the abovementioned scientific evidence, we expect that the stimulation of the central nervous system by the augmented feedback generated by robot-assisted therapy, during the neuromodulation window induced by PAS, can promote a cortical reorganisation which in turn results in a clinical improvement. Therefore, the combination of the two approaches should generate a boost effect on functional motor recovery of UL.

## Trial status

Participant enrolment began on 19 August 2022. The trial is ongoing; the estimated study completion date is October 2023.

## Data Availability

Further information or data can be required from the corresponding author.

## Abbreviations

AEs: Adverse events
ANOVA: Analysis of variance
BBT: Box and Block Test
CTC: Clinical trial centre
Ctrl: Control group
EEG: Electroencephalography
Exp: Experimental group
FMA-UE: Fugl-Meyer assessment scale for upper extremity
M1: Primary motor cortex
NIBS: Non-invasive brain stimulation
PAS: Paired associative stimulation
PLV: Phase locking value
PPC: Posterior-parietal cortex
RAT: Robot-assisted training
rMT: Resting motor threshold
TEPs: Transcranial evoked potentials
TMS: Transcranial magnetic stimulation
TRSP: TMS-related spectral perturbation
UL: Upper limb
